**Methods:**

Eligible participants (*n* = 460) will be recruited via online advertisement in Beijing, China. They will be randomly assigned to receive either quitline-based treatment (QT, *n* = 230) or WQ modality-based treatment (WQ, *n* = 230) using a block randomization method. Participants in the QT group will receive telephone-assisted treatment over a four-week period (multi-call quitline protocol), while those in the WQ group will receive integrated interventions based on the WQ modality for four weeks. A four-week supply of nicotine replacement therapy (gums) will be provided to all participants. Participants will be asked to complete phone or online follow-up at 1, 3, 6, and 12-months. At 1-month follow-up, individuals with self-reported smoking abstinence for more than 7 days will be invited to receive an exhaled carbon monoxide (CO) test for biochemical validation. The primary aim is to determine whether the WQ modality is effective in assisting smokers in quitting smoking. The secondary aims are to evaluate the acceptability, satisfaction, and cost-effectiveness of the WQ modality.

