### Participants and recruitment

Participants will be Chinese smokers. The inclusion criteria are: 1) 18–65 years of age; 2) smoked at least 100 cigarettes in lifetime; 3) currently smoke at least 5 cigarettes per day; 4) willing to make a quit attempt within 1 month; 5) possess a smartphone and a WeChat account, and could operate WeChat app skillfully; 6) promise to complete follow-up on time. Exclusion criteria include: 1) difficulty in understanding the questionnaire; 2) acute exacerbation of chronic cardiopulmonary disease; 3) having received coronary surgical interventions (such as coronary angiography, percutaneous coronary interventions, etc.) in the last month or will receive these interventions in the next month; 4) discharge within 1 month; 5) medical conditions that preclude the use of nicotine replacement therapy (NRT); 6) currently using smoking cessation medications or other aids, including NRT, bupropion, varenicline, electronic cigarettes and other mHealth-based tools, such as web, SMS texting, apps, etc.; 7) being enrolled in another smoking cessation study.

Eligible participants will be recruited through online advertisement. Individuals who are interested in participating will screen a Quick Response (QR) cord to complete a screening questionnaire to ascertain their eligibility for the study. Eligible individuals will be provided an electronic consent (e-consent) form online. After reading the e-consent, they should click the agree button at the end of the form to indicate their consent to participate in the study. The participant recruitment has been started since December 15, 2022, and is ongoing.

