##### WQ modality-based treatment

The WQ modality integrated three WeChat app-based cessation services, including the QUIT WeChat mini program (WMP), the QUIT WeChat group (WG), and the QUIT WeChat official account (WOA). Screenshots of these services have been shown in our previous study [18]. They are developed based on the I-CET model and connected with each other [18]. Since the target population is smokers who plan to quit in the next month, the WQ modality is mainly aimed at the stages of preparation, action, and maintenance, which are focus on motivating to quit, building skills for coping with smoking cravings, and preventing relapse, respectively.

The QUIT WMP is an application function module embedded in the WeChat app [24] (similar to cessation apps [25–27]), which could assist smokers in developing the capacity to quitting smoking and motivating them to do so. It was developed based on the behavior change techniques (BCTs) [28], and smoking cessation treatment guidelines [10, 29]. The detailed description of its functions is shown in Table 1. In addition, the QUIT WMP will automatically send stage-matched short messages, articles or videos via the WeChat app to the users once a day for 4 weeks from the quit date. A list of weekly topics and examples of messages is shown in Table 2. It can be accessed by scanning a QR code (Additional file 2) or searching Chinese ‘Jie Yan You Dao’ in the WeChat app without downloading or installing [24]. The QR code and introduction video of the QUIT WMP will be sent to the participants via the WeChat app after allocation. To increase the participants’ adherence of using the QUIT WMP, daily usage reminders messages will be sent in the WeChat group. Moreover, we will download the participants’ usage data of the QUIT WMP every week, and remind those who use the program less than 5 days per week by telephone.

**Table 1 Tab1:** Detailed description of functions of the QUIT WeChat mini-program

Functions	Sub-functions	Description
Registration	Recording current smoking behavior	Record amount smoked, smoking duration, price of cigarettes, tar content of cigarettes, pattern of smoking behavior, etc
	Recording past history of quit attempts	Record number and duration of past quit attempts
	Testing the level of nicotine dependence	Provide a standardized test to help users assess their level of nicotine dependence
	Assessing quitting readiness	Assess motivation to quit and the stage of smoking cessation

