	Barrier identification and problem solving	Help users to identify the barriers (e.g. nicotine withdrawal symptoms, stress, etc.) that might make it harder to stay off cigarettes and provide personalized suggestions according to the barriers (e.g. how to deal with withdrawal symptoms, eliminate stress, and obtain social support, etc.)
	Strengthening ex-smoker identity	Encourage those who have quit smoking to construct a new identity as never smokers
	Preventing relapse	Provide users information about how relapses occur and to provide coping skills for preventing relapses
Medication reminder	Assessing medication(s) using experiences	Assess usage, side effects and benefits experienced of medication(s) that the smoker is currently using
	Setting a medication use plan	Set the daily time and amount of medication use
	Medication use reminder	Remind users to take medication on time
Additional supports	Quitline	Give information about tobacco quitline ([name]), and develop the “One Click Call” function
	Smoking cessation clinic	Provide online appointment of smoking cessation clinic
	Online consultation	Provide the link of QUIT WeChat group to obtain real-time online consultation
	Online self-help materials	Offer the link to QUIT WeChat official account to obtain online self-help materials for smoking cessation
Users Information	Quitting information	Such as duration of quitting and the number of attempts to quit
	Motivation to quit	Reason for quitting smoking
	Achievements	Virtual medals and accumulate points

**Table 2 Tab2:** The WQ^a^ modality-based treatment by week

Week	Stage	Topic	Example of messages automatically sent by the QUIT WMP^b^	Interventions in the QUIT WG^c^			
				**Group interventions**	**Topic discussion**	**Quit tasks**	**The QUIT WMP functions recommended to use**
Week 1	Preparation	Motivating to quit	Why do you want to quit smoking? Please write your reasons and put it where you can see it every day	Health hazards of smoking and benefits of quitting smoking	Why do I quit smoking?	Sending a screenshot of using the QUIT WMP in the online group every day	Reducing smoking Quitting diary
Week 2	Action	Setting a quit day	Please choose a date as the quit day, such as birthday, holiday, anniversary, etc	Facilitating a quit plan	Why did I fail to quit smoking in the past and how to deal with it this time?	Setting a quit day and announcing a quit declaration in the online group	Facilitating action plan Recording quitting Coping with cravings

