#### Follow-up measures

All participants will complete 1-, 3-, 6-, and 12-month follow-up assessments over the phone or online using the Tencent Questionnaire platform at participants’ convenience. Three non-participating staff will conduct the telephone follow-ups. The follow-up assessment information includes smoking status, quitting attempts, acceptability and satisfaction of the cessation services, and the usage of smoking cessation services, etc. A scale of 0 to 10 (0: not at all; 10: very high) for acceptability and satisfaction with each service will be evaluated. Participants who report quitting smoking or reducing their consumption of cigarettes will fill out the Minnesota Nicotine Withdrawal Scale (MNWS) [40] and the Brief- Questionnaire of Smoking Urges (QSU Brief) [40]. Adverse events and other unintended effects of interventions during the intervention period will be spontaneously reported. At 1-month follow-up, individuals with self-reported smoking abstinence for more than 7 days will be invited to participate in an exhaled carbon monoxide (CO) test for biochemical validation. To increase follow-up compliance, participants will receive 100 RMB (approximately US $ 14.95) in the form of the WeChat red packet (Hongbao, which is similar to an electronic cash reward [41]). The full list of measurements is presented in Table 3.

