**Table 3 Tab3:**
[figure not shown]
SPIRIT flow diagram of enrollment, interventions, and assessments

^a^WQ modality, “Way to Quit” modality

^b^FTND, Fagerstrӧm test for nicotine dependence

^c^MNWS, Minnesota Nicotine Withdrawal Scale

^d^QSU Brief, Brief-Questionnaire of Smoking Urges

^e^NRT, Nicotine replacement therapy

^*^Only for participants who have quit smoking or reduced the cigarette consumption

^#^Only for participants with self-reported smoking abstinence for more than 7 days

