#### Outcomes

The primary outcome is biochemically validated 7-day point prevalence of abstinence (PPA) at the 1-month follow-up [42], defined as the proportion of smokers who self-report not even a puff of smoke in the past 7 days at the 1-month follow-up and are confirmed by a carbon monoxide level in expired air of less than 3 parts per million (ppm) [43].

Secondary outcomes include self-reported 7-day PPA [42] at the 1-, 3-, 6-, 12-month follow-up, self-reported continuous smoking abstinence rate (defined as the proportion of participants who are smoking less than 5 cigarettes [42]) from the 1-month to 12-month follow-up, self-reported quit attempts rate (defined as the proportion of participants who are continuously smoking but have tried to quit smoking for at least 24 h [44]) at the 1-, 3-, 6-, 12-month follow-up, acceptability and satisfaction scores of the services, incremental cost-effectiveness ratio (ICER) of the services.

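### The carbon monoxide test is offered only above 7 days of abstinence, although the primary outcome it confirms needs only 7 days

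*Protocol article*

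**What the plan says.** The Outcomes section defines a primary success by two conditions that must both hold. The participant must "self-report not even a puff of smoke in the past 7 days at the 1-month follow-up and are confirmed by a carbon monoxide level" under 3 ppm.

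The rule for who is offered the CO test appears in three places, each time with a stricter threshold:

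- Follow-up measures: "individuals with self-reported smoking abstinence for more than 7 days will be invited to participate in an exhaled carbon monoxide (CO) test".
- Abstract, Methods: "individuals with self-reported smoking abstinence for more than 7 days will be invited to receive an exhaled carbon monoxide (CO) test".
- Table 3 footnote: "Only for participants with self-reported smoking abstinence for more than 7 days".

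The Statistical analysis plan section treats participants who are lost to follow-up, or who decline validation, as continuing smokers. It does not mention participants who were never invited.

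On message timing, the section on WQ modality-based treatment says the mini program sends its stage-matched messages "once a day for 4 weeks from the quit date". Table 2 lays the programme out over four weeks, and its week 2 example from the same automatic messages reads "Please choose a date as the quit day".

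**The concern.** The test is one half of the primary endpoint, so the rule for offering it should admit everyone who satisfies the other half. As written, it leaves out those at the boundary. A participant recorded at exactly 7 smoke-free days would count in the secondary outcome (self-reported 7-day abstinence at 1 month) but could not count in the primary one, because the reading was never taken. No later analysis decision can repair that.

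At stake is a small downward shift in the confirmed abstinence rate, and with it a small loss of power on the only primary comparison. The article says recruitment was ongoing, so the wording could still be corrected for participants not yet at their 1-month visit.

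The message schedule is a separate matter. A series that begins on the quit date cannot, in its second week, ask the participant to choose that date.

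**Working it through.** **1. The two rules side by side, with abstinence in whole days**

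| Smoke-free days at 1 month | Meets self-report part | Invited to CO test | Can be a primary success |
|---|---|---|---|
| 6 or fewer | no | no | no |
| exactly 7 | yes | no | no |
| 8 or more | yes | yes | yes, if CO is below 3 ppm |

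Only the middle row is in conflict.

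**2. The plan's own sample size**

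Inputs from Sample size: 20% in the quitline (QT) arm, 15 points more in the WQ arm (35%), two-sided 0.05, power 90%, dropout 20%, 230 per arm. With a pooled-variance two-proportion test and no continuity correction:

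n = [1.960·√(2·0.275·0.725) + 1.2816·√(0.20·0.80 + 0.35·0.65)]² / 0.15² = 184.1, rounded up to 185 per arm.

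Allowing for dropout, 185/0.80 = 231.25, so 232 per arm, against the stated 230. The plan's figure is reproduced to within 1%. At 230 × 0.80 = 184 per arm, power is 90.0%.

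**3. Share at exactly 7 days (assumption)**

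The protocol gives no distribution of quit timing. Assume that, among 7-day abstainers, the quit day is evenly spread from some first day *a* to the last day that still allows 7 smoke-free days. Assume also a visit at day 28 or day 30 after allocation. The share at exactly 7 days is then 1/(visit day − 7 − *a* + 1).

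| Quitting starts on | Visit day 28 | Visit day 30 |
|---|---|---|
| day 0 | 1/22 = 4.5% | 1/24 = 4.2% |
| day 7 | 1/15 = 6.7% | 1/17 = 5.9% |
| day 14 | 1/8 = 12.5% | 1/10 = 10.0% |

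The first two rows give the 4–7% range. The third supposes that nobody quits in the first two weeks and is shown only as an outer case.

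In people, on the plan's rates and 184 followed per arm, there are 184 × 0.20 = 36.8 abstainers in QT and 184 × 0.35 = 64.4 in WQ. Shares of 1/24 to 1/15 make that 1.5 to 2.5 people in QT and 2.7 to 4.3 in WQ.

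**4. Effect on power if the same share is lost in both arms**

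Replace 20% and 35% by 0.20(1 − f) and 0.35(1 − f), with 184 per arm:

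Power = Φ{[Δ√184 − 1.960·√(2·p̄(1 − p̄))] / √(p₁(1 − p₁) + p₂(1 − p₂))}

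| Share lost, f | Rates | Difference (points) | Power |
|---|---|---|---|
| 0 | 20.0% v 35.0% | 15.0 | 90.0% |
| 4.2% | 19.2% v 33.5% | 14.4 | 88.2% |
| 6.7% | 18.7% v 32.7% | 14.0 | 87.1% |
| 10% (outer case) | 18.0% v 31.5% | 13.5 | 85.4% |
| 12.5% (outer case) | 17.5% v 30.6% | 13.1 | 84.1% |

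This is a plain two-proportion calculation. The planned analysis is logistic regression, so the figures are approximate.

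**5. The message schedule**

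Count days from the start of the four-week WQ programme, so that week 2 is days 8–14. Twenty-eight daily messages starting on a quit day in that week end between day 8 + 27 = 35 and day 14 + 27 = 41. That is 7 to 13 days after the programme ends on day 28. Starting on the quit date, ending with a four-week programme and choosing the quit day in week 2 cannot all hold.

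**The case against.** The best defence is that the two rules mean the same thing. In continuous time, no puff in the past 7 days means that the last puff was at least 7 days ago, which is hardly different from more than 7 days. If the questionnaire asks a yes/no question about the past week, staff may simply invite everyone who answers no. The stricter phrase may be loose wording. This defence stands in part: the boundary group exists only if abstinence is recorded in whole days and the rule is applied literally, and the article settles neither. But the phrase appears three times, and staff following it as written would leave that group untested.

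It is also fair that the analysis section does not name uninvited participants as smokers. That does not rescue them, because the Outcomes section makes CO confirmation a condition of success.

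A reader might infer more than the document supports:

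- **That the message schedule costs abstainers their success.** It does not. Neither the outcome definition nor the invitation rule refers to messages, and a participant still receiving them can be a confirmed success.
- **That late quitters are misclassified.** Entry requires only that a smoker be "willing to make a quit attempt within 1 month", so some may quit shortly before the visit. Someone with fewer than 7 smoke-free days is not a 7-day abstainer under the protocol's own definition.
- **That the primary comparison is biased between arms.** The invitation rule is the same in both arms, both prepare before the quit date, and nothing shown indicates a different share at the boundary.
- **That the 1-month visit has no time origin.** The text shown does not state one, but Fig. 1 and the body of Table 3 are not available here and may do so.

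**Conclusion.** The invitation rule is stricter than the outcome it serves, and the mismatch is a genuine but minor definition error in the primary endpoint. It affects only participants recorded at exactly 7 smoke-free days. Its size cannot be read from the protocol. The estimate of about 4–7% of 7-day abstainers, with power near 87–88% in place of 90%, rests on an assumed even spread of quit days, a visit at day 28 or 30 after allocation, whole-day recording, and equal loss in both arms. The sample size itself is not in error.

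The conflict over when the WQ messages start is a second, independent inconsistency. It has no bearing on who is tested or counted. Whether the messages also run past the 1-month visit depends on that visit's origin, so nothing is concluded on it here.

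**What to change.** In the Abstract, Follow-up measures and the Table 3 footnote, replace the threshold with the outcome's own criterion: invite to the CO test every participant who meets the self-reported 7-day abstinence definition in Outcomes, that is, 7 days or more. The cost is a few extra CO tests, on the assumptions above roughly two in QT and three to four in WQ. The sample size and the analysis do not change.

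Separately, reconcile the section on WQ modality-based treatment with Table 2 on when the daily messages start and end relative to the quit date and the four-week programme. Which schedule is intended is for the investigators to state. This is a clarification of text only.

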**Table 3 Tab3:**
[figure not shown]
SPIRIT flow diagram of enrollment, interventions, and assessments

^a^WQ modality, “Way to Quit” modality

^b^FTND, Fagerstrӧm test for nicotine dependence

^c^MNWS, Minnesota Nicotine Withdrawal Scale

^d^QSU Brief, Brief-Questionnaire of Smoking Urges

^e^NRT, Nicotine replacement therapy

^*^Only for participants who have quit smoking or reduced the cigarette consumption

^#^Only for participants with self-reported smoking abstinence for more than 7 days

#### Service usage data

Service usage data will also be downloaded from the WeChat app and quitline platforms on a weekly basis during the intervention period. The QUIT WMP utilization metrics (registration, logins) will be extracted from host servers; participation in the QUIT WG (e.g., retention time and the number of messages sent) will be extracted. Telephone counsellors used a web-based tool to record the number, duration and content of calls.

#### Cost data

The cost of each service will be recorded through questionnaire, staff recording, and interview, including direct operating expenses (e.g., salary of staff members and materials used for the interactive activities and training of counselors), costs for hosting the quitline and WeChat-based services, technical support and recruitment costs (which consist of both advertising costs in web-based and offline media, as well as the costs of printing promotional material), and costs for promoting intervention delivery (e.g., rewards for participating in the interactive activities in the QUIT WG).

#### Outcomes

The primary outcome is biochemically validated 7-day point prevalence of abstinence (PPA) at the 1-month follow-up [42], defined as the proportion of smokers who self-report not even a puff of smoke in the past 7 days at the 1-month follow-up and are confirmed by a carbon monoxide level in expired air of less than 3 parts per million (ppm) [43].

Secondary outcomes include self-reported 7-day PPA [42] at the 1-, 3-, 6-, 12-month follow-up, self-reported continuous smoking abstinence rate (defined as the proportion of participants who are smoking less than 5 cigarettes [42]) from the 1-month to 12-month follow-up, self-reported quit attempts rate (defined as the proportion of participants who are continuously smoking but have tried to quit smoking for at least 24 h [44]) at the 1-, 3-, 6-, 12-month follow-up, acceptability and satisfaction scores of the services, incremental cost-effectiveness ratio (ICER) of the services.

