### Sample size

The sample size calculation is based on the primary aim of comparing biologically verified 7-day PPA between the QT group and the WQ group at the 1-month follow-up. We used the following assumptions: (1) significance level of 0.05 for a two-sided test; (2) statistical power of 90%; (3) biologically verified 7-day PPA at the 1-month follow-up in the QT group is conservatively estimated as 20% based on the data from California Smokers’ Helpline [19]; (4) an increase in abstinence rate of 15% in the WQ group compared with the QT group; (5) a dropout rate of 20%. Considering the random block size (4 or 6), 460 eligible patients (230 for each group) will be required in this study.

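### The quit-attempt outcome leaves out everyone who has succeeded, so at equal attempt rates the arm with more abstinence scores worse

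*Protocol article*

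**What the plan says.** The Outcomes section of the protocol article lists, among the secondary outcomes at 1, 3, 6 and 12 months, a self-reported quit-attempt rate "defined as the proportion of participants who are continuously smoking but have tried to quit smoking for at least 24 h". The same section bases the primary outcome on participants who "self-report not even a puff of smoke in the past 7 days at the 1-month follow-up", with carbon monoxide confirmation. Self-reported 7-day abstinence is a secondary outcome at the same four visits.

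No other section adds abstinent participants back into the quit-attempt numerator, gives a different definition, or restricts the measure to a description of non-quitters. The Statistical analysis plan section names the outcomes for logistic regression, and quit attempts are not among them. It also treats participants lost to follow-up as continuing smokers, without saying whether they count as having attempted.

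The Background states the hypothesis that WQ raises abstinence relative to the quitline. The inclusion criteria require at least 5 cigarettes a day at entry and readiness to try quitting in the coming month. Under Follow-up measures, smoking status and quit attempts are collected from all participants at every visit.

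**The concern.** A quit-attempt rate is normally read as a measure of how many people a treatment prompts to try. Here a participant enters the numerator only by trying and then smoking again. Everyone enrolled smokes daily, so anyone with seven smoke-free days at follow-up has gone at least 24 hours without smoking since baseline. The definition therefore removes exactly the successful attempts.

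Membership of the numerator depends on a post-randomisation event that the trial expects treatment to change. A gain in abstinence then pulls the quit-attempt rate down, and a trial that succeeds on its primary outcome could show an apparent deficit in quit attempts that comes from the definition alone.

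**Working it through.** **Inputs from the Sample size section.** "significance level of 0.05 for a two-sided test"; "statistical power of 90"%; 1-month validated abstinence "in the QT group is conservatively estimated as 20"%; "an increase in abstinence rate of 15% in the WQ group compared with the QT group", hence 35% in WQ; "a dropout rate of 20"%; "460 eligible patients (230 for each group) will be required in this study".

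**Reproducing the plan's figure.** The two-proportion formula with pooled variance under the null and mean rate 0.275 gives

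n = [1.960 × √(2 × 0.275 × 0.725) + 1.282 × √(0.20 × 0.80 + 0.35 × 0.65)]² / 0.15² = 184.1, so 185 per arm.

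Inflating for dropout, 185 / 0.80 = 231.25, so 232 per arm against the stated 230. The stated size reproduces closely, which confirms that 20% and 35% are the rates the plan works with. The protocol gives no figure for the quit-attempt outcome.

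**The outcome as written.** Let A be the share of an arm with any attempt of at least 24 hours since baseline, and S the share abstinent at the visit. S is a subset of A.

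- Over all participants, the outcome is A − S.
- Over continuing smokers only, it is (A − S) / (1 − S).

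A is not in the documents, so it is assumed equal in both arms and varied. S is set to the planned 20% and 35%. For the second denominator, the arms have 230 × 0.80 = 184 and 230 × 0.65 = 149.5 expected smokers.

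| Assumed A, both arms | All participants: QT | All participants: WQ | Chance of a significant result against WQ (230 per arm) | Continuing smokers: QT | Continuing smokers: WQ | P at these rates |
|---|---|---|---|---|---|---|
| 50% | 30% | 15% | 97.3% | 37.5% | 23.1% | 0.005 |
| 60% | 40% | 25% | 93.2% | 50.0% | 38.5% | 0.035 |
| 70% | 50% | 35% | 90.5% | 62.5% | 53.8% | 0.11 |
| 80% | 60% | 45% | 89.9% | 75.0% | 69.2% | 0.24 |
| 90% | 70% | 55% | 91.6% | 87.5% | 84.6% | 0.45 |

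**Worked row, A = 70%.**

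- All participants: 70 − 20 = 50% in QT and 70 − 35 = 35% in WQ. The odds ratio is (0.35/0.65) / (0.50/0.50) = 0.54, and z = 0.15 / √(2 × 0.425 × 0.575 / 230) = 3.25, P about 0.001.
- Continuing smokers: 50/80 = 62.5% and 35/65 = 53.8%. The pooled rate is (115 + 80.5) / 333.5 = 0.586, and z = 0.0865 / √(0.586 × 0.414 × (1/184 + 1/149.5)) = 1.60, P about 0.11.

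**When the reversal disappears.**

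- Over all participants, break-even needs A in WQ to equal A in QT plus 15 points, for example 75% against 60%. This is impossible once A in QT exceeds 85%.
- If WQ raises attempts from 60% to 70%, it still scores lower: 70 − 35 = 35% against 60 − 20 = 40%. If it raises them from 60% to 80%, it scores higher: 45% against 40%.
- Over continuing smokers, break-even at A = 60% in QT is 0.35 + 0.65 × 0.50 = 67.5% in WQ, so a rise to 70% already removes the reversal there (53.8% against 50.0%).

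**With abstainers counted as having attempted.** The outcome is A in each arm, and equal attempt rates give equal scores.

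**The case against.** A reader might infer that a better treatment must score worse, or that this trial will report fewer attempts on WQ. The documents do not support that. Equal attempt rates are an assumption. WQ spends its first two weeks on motivation and on setting a quit day, and the quitline sessions also plan a quit date, so the protocol does not settle which arm prompts more attempts. The common rate is not in the documents either, which is why a range is shown.

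A reader might also infer a statistically significant result against WQ. That holds over the whole range only with all participants as denominator. With continuing smokers, the gap is not significant at attempt rates of 70% or more, and high rates are plausible because entry requires readiness to try within a month. The definition's reference to participants points to the first denominator, but the second is a possible reading. It does not rescue the measure: the direction is still reversed at equal attempt rates, and the comparison is between groups selected after randomisation.

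Further points stand. No test of this outcome is named, so the P values above are illustrative. The 20% and 35% are carbon monoxide-validated 1-month rates standing in for self-reported status, and no rates are given for later visits, so the size is shown for 1 month only.

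Finally, if both outcomes are taken over all participants, adding self-reported 7-day abstinence to this rate roughly recovers total attempts. The measure could then be read as a failed-attempt category beside abstinence. That is fair, but it is named a quit-attempt rate and listed as an outcome in its own right, and nothing in the protocol tells the reader to combine the two.

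**Conclusion.** The concern holds as a defect of definition in one secondary outcome. Successful attempts are excluded, and the outcome is conditioned on not being abstinent. At equal total attempt rates the arm with more abstinence scores lower.

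At the planned 1-month abstinence rates and a common attempt rate assumed between 50% and 90%, the shortfall for WQ is 15 points over all participants. Among continuing smokers it runs from about 14 points (37.5% against 23.1%) down to about 3 (87.5% against 84.6%). Over all participants, the reversal disappears only if WQ raises total attempts by more than it raises abstinence.

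The primary outcome, its analysis and the sample size are unaffected. This is a should-fix.

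**What to change.** Define the outcome as the proportion of all randomised participants with at least one quit attempt of 24 hours or more since baseline. Count those abstinent at the assessment as having attempted, and those lost to follow-up as having made no attempt.

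The window should run from baseline and not from the previous visit. Someone abstinent since month 1 makes no new attempt between months 6 and 12, and counting abstainers per interval would record attempts that did not occur.

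If the present measure is kept, name it failed attempts, show it beside 7-day abstinence over the same denominator, and mark it as descriptive, not as a between-arm comparison of effectiveness.

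The cost is a change of wording. Smoking status and quit attempts are already collected from everyone at each follow-up.
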